### Primary variables

#### Maternal characteristics

|                                         |                    |
|-----------------------------------------|--------------------|
| Maternal age (years: mean/range) |                    |
| Age range                        | 18-24              |
|                                         | 25-34              |
|                                         | 34-49              |
| Ethnicity                        | White European     |
|                                         | Latino Americans   |
|                                         | Black non-Hispanic |
|                                         | Asian non-Hispanic |
|                                         | Arab               |
| Nulliparous                      |                    |
| Smoking                          |                    |
| ICU admission                    |                    |
| COVID 19 diagnosis date          |                    |
| Delivery <37 weeks            |                    |

#### Maternal comorbidities

|                                     |                                        |
|-------------------------------------|----------------------------------------|
| Obesity (BMI> 30 kg/m2)   |                                        |
| Cardiovascular comorbidities | Chronic Cardiac Disease                |
|                                     | Pre-pregnancy HT                       |
| Pulmonary comorbidities      | Chronic Pulmonary Disease (not asthma) |
|                                     | Asthma                                 |
| Hematologic comorbidities    | Chronic Blood Disease                  |
|                                     | Thrombophilia                          |
|                                     | Antiphospholipid syndrome              |

#### COVID-19 symptoms

|                                                   |                                 |
|---------------------------------------------------|---------------------------------|
| Mild symptoms (Symptoms reported at birth) | Cough                           |
|                                                   | Fever                           |
|                                                   | Dyspnoea                        |
|                                                   | New olfactory or taste disorder |
|                                                   | Fatigue/malaise                 |
|                                                   | Altered consciousness           |
|                                                   | Headache                        |
|                                                   | Nausea/vomiting                 |
|                                                   | Diarrhoea                       |
| Mild-moderate pneumonia                    |                                 |
| Severe pneumonia                           |                                 |
| Septic shock/maternal mortality            |                                 |

#### Delivery Type

|                                |
|--------------------------------|
| Premature rupture of membranes |
| Preterm PRM                    |
| NICU admission                 |

|                        |
|------------------------|
| NICU admission days    |
| Postpartum haemorrhage |
| Abruptio placentae     |
| Severe Preeclampsia    |
| HELLP                  |
| Pulmonary embolism     |

The rest of the variables are described in appendix 5

### Statistics

For the descriptive analysis, categorical variables were expressed as absolute and relative frequencies; whereas quantitative ones were expressed as mean and range (minimum-maximum values). Analysis of the possible association of both the characteristics of the patients and the *outcomes* collected with COVID-19 infection is carried out using the Pearson Chi-square test or Fisher's exact test and the Mann-Whitney U test (after checking the absence of normal data using the Kolmogorov-Smirnov test). See sections of Data Quality Plan and sample size. Statistical significance was established with  $P < 0.05$ . All statistical analyses were carried out with SAS 9.4 software.

For each response variable (*outcome*) a multiple logistic regression model has been carried out, refined with the backward conditional stepwise method.

The response variables are those described in the previous section. The subset of explanatory variables is different for each model and is specified in the text.

It will only be of interest the Odds Ratio (OR), its 95% CI and the significance of the “COVID” factor. The information on the rest of the explanatory variables is irrelevant since they only act as adjustment variables.

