### Patients

Case eligibility criteria included individuals with laboratory confirmation of COVID-19 infection, irrespective of clinical signs and symptoms or the result of another serological test. Positive RNA PCR test from maternal nasopharyngeal swabs.

The selection of the control group will be collected in the same database, considering patients with negative COVID-19 delivery diagnosed by PCR screening at the time of delivery or less than 3 days before.

The delivery or deliveries that were treated in this site and that occurred within the same day, before and after the case (maximum 3 per case), are included in the control group. If the case were the last delivery of the day, the first ones of the following day could be recruited. If the case were the first of that day, the last one of the previous day could be recruited.

The data collected will be entered at the time they join the registry.

Delivery monitoring: the *outcomes* include perinatal and neonatal events, which were collected at the time of delivery and the days immediately afterward. These perinatal events included gestational age, type of delivery, presence of prepartum or premature rupture of membranes before delivery, as well as any medical complications (thromboembolic events, admission to ICU, maternal death) and obstetric complications (hemorrhagic events and hypertensive disorders), while neonatal events included the 5-minute Apgar score, the pH of the umbilical artery and possible complications such as admission to the NICU and neonatal death in the follow-up period or intrauterine foetal death. The definitions of obstetric pathology follow the international criteria of the ACOG and RCOG (18-21).

Follow-up after delivery: Patient follow-up is carried out by the local investigator over the phone and the medical history is consulted from the time the patient is discharged up to 6 weeks later in order to detect late postpartum complications related to COVID 19. In the case of the new-born, the follow-up is 14 days by the investigating neonatology department by telephone and consultation of the patient's medical history to detect symptoms of COVID 19 symptoms. Complications recorded in the mother during this period (mastitis, endometritis, pulmonary embolism) as well as neonatal death or readmission of the new-born due to COVID were considered *outcomes* of interest and analysed together with those described above.

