## Statistics

For the statistical analysis, the SAS v9.4 software will be used.

The set of groups of variables requested and collected for each enrolled patient will be the same. The demographic and clinical characteristics of the population included will be summarized. Mean, standard deviation, minimum and maximum or median and interquartile intervals will be used for continuous variables, according to the distribution. The corresponding absolute and relative frequency will be reported for the discrete variables.

The possible association of both the characteristics of the patients and the *outcomes* collected with COVID-19 infection using the Pearson Chi-square test or Fisher's exact test and the Mann-Whitney U test (after checking the absence of normal data using the Kolmogorov-Smirnov test). Statistically significant associations were considered when the p value was less than 0.05. For those categorical variables in which statistically significant differences were identified, the corresponding Odds Ratio (OR) and 95% Confidence Intervals (95% CI) were estimated using univariate logistic regression models.

Logistic regressions, both univariate and multivariate, will be performed, determining the odd ratio and its 95% confidence interval.

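### Substudy 3 lets backward stepwise elimination choose the adjustment variables for the COVID odds ratio, and Substudy 4 gives two conflicting rules on which odds ratios are estimated

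*Protocol*

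**What the plan says.** **Substudy 3, Statistics.** One logistic model is planned per outcome: "a multiple logistic regression model has been carried out, refined with the backward conditional stepwise method". The target is narrow: "It will only be of interest the Odds Ratio (OR), its 95% CI and the significance of the" COVID factor. Of the other terms it says "The information on the rest of the explanatory variables is irrelevant since they only act as adjustment variables". The candidate covariates may vary: "The subset of explanatory variables is different for each model and is specified in the text". No removal threshold is given, and no term is named as always kept. The significance level is 0.05, with sidedness not stated.

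**Substudy 4, Statistics.** After the association tests comes this rule: "For those categorical variables in which statistically significant differences were identified, the corresponding Odds Ratio (OR) and 95% Confidence Intervals (95% CI) were estimated", by univariate logistic regression. The filter is the 0.05 level: "Statistically significant associations were considered when the p value was less than 0.05". The sentence that follows plans univariate and multivariate logistic regressions with odds ratios and 95% intervals, and sets no significance condition. The only objective listed for Substudy 4 is prevalence.

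**The concern.** Substudy 3 asks whether infected women have more obstetric morbidity, and the adjusted COVID odds ratio for each outcome is its answer. A covariate belongs in such a model because it confounds the comparison. Backward elimination uses another test: whether the covariate significantly predicts the outcome in this sample. A covariate strongly linked to infection and moderately linked to the outcome can fail that test and still bias the COVID estimate. The risk is greatest for rare outcomes on the protocol's list, such as HELLP or pulmonary embolism. The final interval is then computed as if the surviving model had been fixed beforehand.

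In Substudy 4, odds ratios shown only when significant are on average too far from 1, because only large estimates pass the filter.

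**Working it through.** The protocol gives no sample size, outcome risk or odds ratio for Substudy 3, so there is no planned figure to reproduce. The check is a simulation on assumed inputs.

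**Inputs for Substudy 3**
- From the protocol: controls are deliveries "before and after the case (maximum 3 per case), are included in the control group". Three controls per case gives 1/(1+3) = 25% exposed. Level 0.05, taken as two-sided.
- Assumed: n = 1000; outcome risk about 8%; eight binary confounders, each with prevalence 20% and log-OR 0.4 with infection; log-OR with outcome +0.3 (same direction) or -0.3 (opposite direction); removal at p > 0.05 or p > 0.10, with a Wald test standing in for the conditional one; 1000 runs per scenario.

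**Why a real confounder is dropped.** The approximate standard error of one confounder's log-OR is 1/√(1000 × 0.08 × 0.92 × 0.20 × 0.80) = 1/√11.8 = 0.29. Then z = 0.3/0.29 = 1.03, and the chance of being kept at 0.05 is Φ(1.03 - 1.96) + Φ(-1.03 - 1.96) ≈ 0.18. So a true confounder with OR exp(0.3) = 1.35 is discarded in about four of five samples. Its prevalence differs between exposed and unexposed by about 0.4 × 0.2 × 0.8 = 0.064. Dropping all eight would therefore shift the log-OR by 8 × 0.3 × 0.064 = 0.154, a factor of 1.17. Selection should land between 1.00 and that.

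**Results with COVID always kept** (geometric mean OR; 95% coverage; rejection rate where the true OR is 1). Ranges span the two removal thresholds.

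| Confounding | True OR | Fixed full model | Backward elimination |
|---|---|---|---|
| Same direction | 1.0 | 0.99-1.01; 94.7-95.0%; 5.0-5.3% | 1.07-1.08; 92.3-92.8%; 7.2-7.7% |
| Same direction | 1.5 | 1.50-1.51; 93.7-95.8% | 1.59-1.62; 91.4-94.4% |
| Opposite | 1.0 | 0.97-0.99; 95.4-95.5%; 4.5-4.6% | 0.88-0.92; 93.5-94.7%; 5.3-6.5% |
| Opposite | 1.5 | 1.49; 94.5-95.4% | 1.35-1.38; 92.8-94.1% |

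Monte Carlo error on a coverage near 95% is √(0.95 × 0.05/1000) = 0.7 points, but both methods were run on the same data sets. Most of the loss comes from an off-centre estimate. In the first row at removal 0.05, the mean standard error was 0.260 against an empirical 0.273 (5% short). The full model had 0.267 against 0.277 (4% short).

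A second simulation used other assumed inputs: 500 cases, 1000 controls, eight moderate same-direction confounders, and removal at p > 0.05. At a true OR of 1 it gave 7.0% rejection, mean OR 1.05 and 93% coverage with COVID kept, against 4.7% and 95% for the full model.

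**If COVID could be removed and its OR were reported only when retained** (first set of inputs):
- True OR 1.5: retained in 26-65% of runs, mean reported OR 1.75-1.94.
- True OR 1.0: retained in 6-12% of runs. Coverage among those was 0% at removal 0.05 and 41-52% at removal 0.10.

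**Substudy 4 filter.** From the protocol: 1056 women, level 0.05. Assumed: prevalence 2-10%, factor frequency among uninfected women 6% or 20%, true OR 1.5.

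With β = ln 1.5 = 0.405, standard error s, δ = β/s and P = Φ(δ - 1.96) + Φ(-δ - 1.96), the mean log-OR among significant results is β + s[φ(1.96 - δ) - φ(1.96 + δ)]/P.
- 10% prevalence, 20% factor: s = 0.234, δ = 1.73, P = 0.41. Mean = 0.405 + 0.234 × 0.388/0.41 = 0.63, so OR 1.87; coverage 93.9%.
- 2% prevalence, 6% factor: s = 0.784, δ = 0.52, P = 0.081. Mean = 0.405 + 0.784 × 0.122/0.081 = 1.59, so OR 4.89; coverage 61.1%.

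Without the filter this bias is zero.

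**The case against.** Several objections deserve weight.

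- **COVID being removable.** A reader might infer that the COVID term can be eliminated. The text does not say so. Interest in the COVID odds ratio from each outcome's model suggests that it stays, and an analysis plan could settle it. This stands: the figures for a removable COVID term are conditional on that reading. What remains is that nothing in the protocol fixes retention.
- **Exaggeration in Substudy 3.** A reader might conclude that stepwise selection inflates the reported odds ratios. With COVID kept, it does not do so in general: opposite-direction confounding pulled a true 1.5 down to 1.35-1.38. Undercoverage is modest.
- **Substudy 4 reporting only significant odds ratios.** The next sentence plans univariate and multivariate odds ratios unconditionally, and the filter sentence covers only univariate odds ratios of categorical variables. This stands: the defect is two adjacent sentences that conflict.
- **Different covariates per outcome.** These are legitimate. One common set is a preference, so varying sets are no fault in themselves.
- **Assumed inputs.** All magnitudes rest on them, and rarer outcomes were not simulated.

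None of this defends the selection rule. It is a stated method, and it does not suit the stated purpose of adjusting one exposure effect.

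**Conclusion.** The point holds in limited form. Substudy 3 fixes a selection method that can drop confounders and gives intervals that ignore the selection. Under the assumed inputs with COVID kept, coverage is about 91-94% and type I error about 7% with same-direction confounding. Bias runs in either direction. The effect is moderate, but it falls on the quantity that answers the substudy's question. Larger distortion in Substudy 3 arises only if COVID could be removed and its odds ratio were then left out, which the protocol neither states nor excludes.

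In Substudy 4 the filter sentence, if followed, would inflate a true OR of 1.5 to between 1.87 and 4.89 on average across the assumed settings. The following sentence contradicts it, and these odds ratios are secondary to prevalence. The change should be made, but the registry's design does not depend on it.

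**What to change.** **Substudy 3, Statistics**
- Delete the stepwise step and state that the COVID term is retained in every model.
- Pre-specify for each outcome a set of pre-infection covariates already collected: for example age, ethnicity, BMI or obesity, parity, smoking, multiple gestation and pre-pregnancy comorbidities. Sets may differ between outcomes.
- Use a smaller set or Firth penalisation where events are sparse.
- Keep the site random intercepts planned under Heterogeneity tests.
- The restriction to pre-infection covariates is a precaution: the substudy's variable tables mix baseline factors with later events such as ICU admission, but the Statistics section does not say that it adjusts for those.

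**Substudy 4, Statistics**
- Delete the significance condition and report the odds ratio and 95% interval for all listed variables, whatever the p-value.

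**Cost.** Wording only, with no new data. Intervals widen somewhat. In the simulation at 8% outcome risk the mean standard error rose by 2-3% (for example 0.267/0.260 = 1.03). For rare outcomes the widening will be greater; that was not simulated.

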## Rationale

To date, few studies have described the impact of the SARS-CoV-2 virus on pregnancy, particularly infection occurring during the third trimester of pregnancy. The impact of the virus during the first and second trimesters of pregnancy remains unknown and must be urgently determined. All current recommendations are based on less than 50 cases published in the literature, with speculations on different aspects of management. To identify moderate effects (such as vertical transmission, foetal death, maternal or neonatal death), larger sample sizes than those currently available are required to allow accurate risk estimates. The national registry for COVID-19 in pregnancy described here is a tool for sharing and centralizing data related to exposures to SARS-CoV-2 during pregnancy in a structured way. It should speed up the process of prospectively obtaining a large unbiased data set and will collect information at national level.

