## Study population and selection criteria

For the characterization of the clinical course of SARS-CoV-2 infection during pregnancy, the pre-study sample size calculation has not been carried out, as registry-based studies generally tend to be comprehensive without involving hypotheses.

Patients eligible for follow-up of target population will be any pregnant woman who is suspected or needs to be ruled out as having a SARS-CoV-2 infection at any time during pregnancy with positive test results for SARS-CoV-2 by PCR.

Information regarding each pregnant woman's demographic characteristics, comorbidities and current obstetric history was extracted from the medical history and the patient interview; subsequently, age and race were categorized according to the classification used by the Center for Disease Control and Prevention (CDC) (17).

For the selection of the control group to be collected in the same database, patients with a negative COVID-19 delivery diagnosed by PCR screening at delivery, or less than 3 days before, were considered.

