## Substudy 3. Cohort study on obstetric pathology.

### Objective/s

The purpose of this study was to test if pregnant patients with COVID-19 have more obstetrical morbidity than those non-infected.

- Determine the variables that are associated with more maternal and neonatal morbidity.
- Quantify the risk of adverse pregnancy outcomes (e.g., miscarriage, stillbirth, growth restriction) and neonatal outcomes (e.g., NICU, prematurity, death, birth defects).

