### Design

Longitudinal cohort case study to quantify the obstetrical and perinatal morbi-mortality throughout all hospitals in Spain with a universal, consecutive PCR based screening program.

Recruitment: 1st March 2020 to 1st March 2021. Spanish sites collected in Appendix 1.

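### Substudy 3 gives one COVID odds ratio for infections at any gestation, with no rule that infection precede the outcome, so for some outcomes it can be biased in either direction

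*Protocol*

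**What the plan says.** **Exposure.** The registry's case definition (Protocol, Definitions) equates the PCR result with exposure or non-exposure. Study population and selection criteria admits "infection at any time during pregnancy with positive test results for SARS-CoV-2 by PCR". Substudy 3, Patients, takes as cases "individuals with laboratory confirmation of COVID-19 infection, irrespective of clinical signs and symptoms" and sets no gestational limit.

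**Setting and controls.** The Design section places Substudy 3 in hospitals "with a universal, consecutive PCR based screening program". Controls are "patients with negative COVID-19 delivery diagnosed by PCR screening at the time of delivery or less than 3 days before".

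**Outcomes.** The objective covers miscarriage, stillbirth, "growth restriction) and neonatal outcomes (e.g., NICU, prematurity, death, birth defects". The Statistics section takes its response variables from the preceding section. The visible tables there include delivery before 37 weeks, preterm rupture of membranes, severe preeclampsia, HELLP, abruption, postpartum haemorrhage, pulmonary embolism and NICU admission.

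**Model.** Each outcome has a multiple logistic regression with backward selection. The Statistics section states "It will only be of interest the Odds Ratio (OR), its 95% CI and the significance of the" COVID factor and calls the other explanatory variables irrelevant except for adjustment.

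**Timing.** "COVID 19 diagnosis date" is among the Substudy 3 maternal variables. Nothing in the protocol says how it enters the models. The Rationale says: "The impact of the virus during the first and second trimesters of pregnancy remains unknown and must be urgently determined".

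**The concern.** A woman whose first positive PCR comes at 37 weeks or later cannot have delivered before 37 weeks, yet she counts as exposed in the model for preterm delivery. Controls are sampled at delivery at whatever gestation that occurs, so they carry no such restriction. Severe preeclampsia and HELLP can already be present when a late PCR turns positive. In these models the COVID factor therefore combines infections that could have acted on the outcome with infections that could not.

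Two things are at stake. The odds ratio for these outcomes may be misread, as false reassurance or as false alarm. And one pooled figure cannot separate the first- and second-trimester impact that the Rationale calls urgent.

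**Working it through.** Substudy 3 states no sample size, event rate or effect size, so there is no figure of the plan's own to reproduce. The calculation below shows only how far, and in which direction, pooling can move the odds ratio.

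**Inputs (all assumed).** Control risk p0 = 5%. True odds ratio for infections early enough to act = 2.0. L = share of cases first positive too late to act.

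**Formulas.**
- Control odds = 0.05/0.95 = 0.05263.
- Early-case odds = 2 × 0.05263 = 0.10526, so early-case risk = 0.10526/1.10526 = 0.09524.
- Pooled case risk = (1 − L) × 0.09524 + L × (late-case risk).
- Pooled odds ratio = odds of the pooled case risk ÷ 0.05263.

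**(a) Late cases carry control risk.** At L = 0.5: risk = 0.5 × 0.09524 + 0.5 × 0.05 = 0.07262, odds = 0.07831, odds ratio = 1.49.

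**(b) Late cases cannot have the outcome**, as with preterm delivery and a first positive PCR at 37 weeks or later. At L = 0.5: risk = 0.04762, odds = 0.05, odds ratio = 0.95.

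| Share late (L) | (a) Odds ratio | (b) Odds ratio |
|---|---|---|
| 25% | 1.74 | 1.46 |
| 50% | 1.49 | 0.95 |
| 75% | 1.24 | 0.46 |
| 90% | 1.10 | 0.18 |

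At L = 50%, a control risk of 2% gives 1.50 (a) and 0.98 (b), and a control risk of 8% gives 1.48 and 0.92.

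**(c) Women with the outcome are tested or infected more often**, so late cases have r times the control odds. With no true effect and L = 0.5, the pooled odds ratio is 1.25 at r = 1.5, 1.49 at r = 2 and 1.95 at r = 3. At r = 2, late-case risk is 0.09524, pooled risk is 0.5 × 0.05 + 0.5 × 0.09524 = 0.07262, and the ratio is 1.49 as in (a).

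The same one-factor model can thus give a value closer to 1 than the truth, a value on the wrong side of 1, or an apparent effect where none exists.

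**The case against.** **The Statistics sentence is about reporting.** It says which coefficient is reported and does not forbid a look at timing; exposure windows are often left to a statistical analysis plan. This is fair, and the text should not be read as a ban. But it does fix one undifferentiated factor as the only result of interest, and a timing covariate would count as mere adjustment.

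**Timing is handled elsewhere.** The Heterogeneity tests section promises attention to differences in exposure and between women, with subgroup analyses and individual-level interactions, so it is not only about differences between sites. Substudy 1 tabulates time from diagnosis to delivery, and Substudy 2 describes gestational age at onset. However, the heterogeneity text never names infection timing, and neither of the other substudies supplies the comparison with uninfected controls that is Substudy 3's task.

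**The Rationale speaks for the whole registry.** It is not a specific promise of Substudy 3. True; it shows what a single pooled odds ratio would leave unanswered.

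**Growth restriction and birth defects may not be modelled.** They appear in the objective but not in the visible variable tables, and Appendix 5 is a separate file. This stands. They belong to the point only if they are modelled.

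**Most listed outcomes are untouched.** Postpartum haemorrhage, NICU admission and other events at or after delivery are largely unaffected. This also stands and limits the point to a subset.

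**Conclusion.** The point holds for delivery before 37 weeks, preterm rupture of membranes, severe preeclampsia and HELLP, and for growth restriction or birth defects if they are modelled. For these, no rule puts infection before the outcome, and the single odds ratio mixes women with different time at risk although the diagnosis date is collected.

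A reader might infer that pooling always dilutes effects towards the null. The documents do not support that. Dilution follows only if late-infected women carry control risk, and for preterm delivery they cannot have the outcome at all, which pushes the ratio below 1. Testing prompted by the outcome pushes it up.

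A reader might also infer that most cases will be detected late. Universal screening makes positives at delivery likely, but the protocol gives no split by gestation.

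The sizes above (a true 2.0 becoming 1.49 or 0.95 with half of cases late) rest wholly on assumed inputs. The missing temporal order does not. Miscarriage raises a different problem, because controls are drawn from deliveries, and is not part of this point.

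**What to change.** In Substudy 3, Statistics:

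1. Replace the yes/no COVID factor with gestational age at first positive PCR: first trimester, second trimester, third trimester before the delivery admission, and detected by delivery screening. Report each against controls.
2. For delivery before 37 weeks and preterm rupture of membranes, compare antenatally detected cases only with controls still pregnant and outcome-free at the gestational age of the case's first positive PCR (delayed entry or risk-set comparison). Exclude cases whose outcome preceded the positive test.
3. Report all women detected by delivery screening, whatever their gestation, as a separate group against delivery-screened controls. Do not move them into the exposed group because they were positive before 37 weeks: among women tested on admission, that keeps only those delivering preterm. For example, assume 100 cases detected earlier and 100 detected at delivery, each with 5% risk and no true effect. The rule yields 105 exposed women with 10 preterm deliveries, and (10/95)/(5/95) = 2.0.
4. If birth defects are analysed, draw no conclusion on them from infections first detected after the first trimester.

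**Cost.** Steps 1 and 3 need only analysis wording, using the diagnosis date and the gestational age at delivery that the protocol already collects. Exposed groups become smaller and intervals wider, and the preterm comparison is more complex. Step 2 needs the date of membrane rupture. The visible lists show no onset date for that or for preeclampsia, HELLP or growth restriction, so check Appendix 5. Where onset is unrecorded, report by timing category and say that the order is unknown. The PCR date marks detection, not infection, and the report should say so.

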## Abstract

**Rationale:** Knowledge about the impact of the SARS-CoV-2 virus on pregnancy is still scarce and all current recommendations are based on less than 100 cases published in the literature. To identify moderate effects (such as vertical transmission, obstetric morbidity, foetal death, maternal or neonatal death) and to allow accurate risk estimates, larger sample sizes than those currently available are required.

**Methods:** Prospective observational study of pregnant women in whom SARS-CoV-2 infection is suspected at any time during pregnancy with positive test results for SARS-CoV-2, in order to create a registry of baseline characteristics of the pregnant woman, aspects related to the course of pregnancy and delivery, and related to the new-born, with an observation period of up to 14 days after delivery. Subsequently, several phased studies will be conducted to help establish and monitor the set of measures to improve the care of pregnant women.

**Discussion:** The national registry for COVID-19 in pregnancy described here is a tool for sharing and centralizing data related to exposures to SARS-CoV-2 during pregnancy in a structured way. It should speed up the process of prospectively obtaining a large unbiased data set and will collect information at national level.

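### Substudy 3 aims to quantify risk, but its only adjusted measure is an odds ratio, which lies further from 1 than the risk ratio for common outcomes and gives no absolute risk

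*Protocol*

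**What the plan says.** The protocol gives Substudy 3 two aims under Objective/s. The first is comparative: to "test if pregnant patients with COVID-19 have more obstetrical morbidity than those non-infected". The second is to "Quantify the risk of adverse pregnancy outcomes" and neonatal outcomes, with miscarriage, stillbirth, growth restriction, NICU admission and prematurity among the examples. The Design section describes a "Longitudinal cohort case study to quantify the obstetrical and perinatal morbi-mortality throughout all hospitals in Spain". The Abstract says that the field needs larger samples "to allow accurate risk estimates".

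Under Patients, cases are women with a positive PCR. Controls are PCR-negative women tested at delivery or less than 3 days before it. They are taken from deliveries at the same site "within the same day, before and after the case (maximum 3 per case), are included in the control group".

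Under Statistics there are two layers. The descriptive layer gives counts and percentages for categorical variables and tests outcomes against infection with chi-square or Fisher's exact tests. The adjusted layer states that for each outcome "a multiple logistic regression model has been carried out, refined with the backward conditional stepwise method". On what is taken from that model it says: "It will only be of interest the Odds Ratio (OR), its 95% CI and the significance", and the sentence goes on to name the COVID factor. The next sentence sets aside the other explanatory variables because they serve only for adjustment.

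**The concern.** The second aim and the Design section ask for a quantity on the risk scale. The adjusted analysis delivers one on the odds scale and nothing else. The protocol evidently thinks adjustment is needed, since it plans a multivariable model for every outcome. The result it relies on most is therefore the one for which no risk is reported.

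Two things are at stake. First, the same odds ratio can stand for very different absolute excess risks, so the adjusted result alone does not tell a clinician how many more women or newborns are affected. Second, the odds ratio is close to the risk ratio only when the outcome is uncommon. The listed outcomes include type of delivery, premature rupture of membranes, NICU admission and delivery before 37 weeks, and the protocol gives no ground for treating these as rare.

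**Working it through.** **Step 1: does the design allow risks to be estimated?** In this protocol a case is an infected woman, not a woman with the outcome (Definitions; Substudy 3, Patients). Sampling is on exposure, with up to 3 unexposed deliveries per exposed woman, and outcomes are recorded afterwards. The design therefore does not force an odds ratio. For events at or after delivery, the risk in each group can be estimated.

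There is one limit. Cases may test positive at any time in pregnancy (Study population and selection criteria), while controls enter at delivery. A control risk of miscarriage cannot come from women sampled at delivery.

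**Step 2: which adjusted measures are named?** For Substudy 3: the odds ratio, its 95% confidence interval and its significance. No adjusted risk, risk difference or risk ratio appears.

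**Step 3: how far apart are the scales?** Substudy 3 states no outcome rate, effect size, power or sample size, so there is no figure of its own to reproduce. The control risks p0 and the effects below are assumptions, chosen to show the range.

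From odds ratio to risk: p1 = OR × p0 / (1 − p0 + OR × p0), RR = p1 / p0, RD = p1 − p0. For example, with OR = 2.0 and p0 = 0.25, p1 = 0.50 / 1.25 = 0.40, so RR = 1.60 and RD = 0.15.

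| Control risk (assumed) | Risk in infected at OR 2.0 | Risk ratio | Risk difference (points) |
|---|---|---|---|
| 1% | 1.98% | 1.98 | 1.0 |
| 2% | 3.92% | 1.96 | 1.9 |
| 5% | 9.52% | 1.90 | 4.5 |
| 10% | 18.18% | 1.82 | 8.2 |
| 25% | 40.00% | 1.60 | 15.0 |
| 40% | 57.14% | 1.43 | 17.1 |

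From a true risk ratio to the odds ratio: OR = [p1 / (1 − p1)] / [p0 / (1 − p0)], with p1 = RR × p0.

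| True risk ratio (assumed) | OR at p0 1% | OR at p0 10% | OR at p0 25% |
|---|---|---|---|
| 0.67 | 0.67 | 0.65 | 0.60 |
| 1.5 | 1.51 | 1.59 | 1.80 |
| 2.0 | 2.02 | 2.25 | 3.00 |

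At control risks of 2% or less and risk ratios up to 2, the two ratios differ by about 2% or less. For risk ratios of 1.5 to 2.0, the odds ratio exceeds the risk ratio by 6% to 12.5% at a control risk of 10%, and by 20% to 50% at 25%. Below 1 the departure runs the other way.

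**The case against.** The strongest reply concerns the word *only*. Read with the sentence that follows, it mainly sets the COVID coefficient against the covariate coefficients in the same model. A reader might infer that the protocol forbids every measure except the odds ratio, but the text does not support that. It states a sound rule, that adjustment coefficients are not to be interpreted, and it leaves out risk measures without excluding them. This stands, and it is a reason to reword the sentence rather than delete it. The odds ratio is still the only adjusted measure named.

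Second, a reader might conclude that no absolute risk will be available at all. That is wrong. Counts and percentages are planned, and crude risks, differences and ratios follow from the outcome-by-infection tables. Only the adjusted versions are missing.

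Third, the odds ratio is a valid measure and serves the first aim, the comparative test. This also stands; the mismatch is with the second aim.

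Fourth, several listed outcomes, such as maternal death, HELLP and pulmonary embolism, may be rare enough for the scale not to matter. Standardised risks for sparse outcomes could also have unstable intervals. Both points limit the scope of the change.

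Finally, standardisation is the kind of detail often left to a statistical analysis plan. But the protocol is not silent here: it names its adjusted measure, and that measure does not match one of its own objectives.

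**Conclusion.** The point holds in a limited form. The adjusted analysis of Substudy 3 does not answer the risk objective on its own scale, although the design allows it for delivery and neonatal outcomes. For outcomes with control risks of about 10% or more the difference is material; at 2% or less it is negligible. One odds ratio of 2.0 corresponds to excess risks from about 1 point (control risk 1%) to 15 points (25%).

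These figures rest on assumed control risks and effects. They also treat all women as sharing one control risk. With covariates in the model the exact risk ratio depends on the covariate mix, which is why it should be estimated by standardisation and not by converting the odds ratio.

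A reader might go further and infer that common outcomes will look worse than they are. The documents do not support this. It would require the odds ratio to be read as a risk ratio and the true effect to be above 1; below 1 the same misreading overstates protection. Nothing in the protocol says that odds ratios will be read as multiples of risk.

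**What to change.** Keep the logistic model, the odds ratio and the rule that covariate coefficients are not interpreted. Reword the Statistics section of Substudy 3 so that, for each binary delivery or neonatal outcome with enough events, the COVID effect is also given as the adjusted risk in each group, the risk difference and the risk ratio, each with a 95% confidence interval. All of these come from the same fitted model by marginal standardisation. State what counts as enough events and which women the risks are standardised over.

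Leave out miscarriage and any other outcome whose risk cannot be estimated from controls sampled at delivery. For sparse outcomes, the odds ratio and the crude risks suffice.

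The cost is a little more analysis from models that are fitted anyway. No new data are needed. The main drawback is unstable intervals if the method is applied to sparse outcomes, which the event threshold is meant to prevent.
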